## Abstract

**Background:**

Māori and Pacific Island people have significantly higher smoking rates compared to the rest of the New Zealand population. The main aim of this paper is to describe how knowledge of Indigenous people’s practices and principles can be combined with proven effective smoking cessation support into a cessation intervention appropriate for Indigenous people.

**Methods/Design:**

A literature review was conducted to identify what cultural principles and practices could be used to increase salience, and what competition elements could have an impact on efficacy of smoking cessation. The identified elements were incorporated into the design of a cessation intervention.

**Discussion:**

Cultural practices incorporated into the intervention include having a holistic family or group-centred focus, inter-group competitiveness, fundraising and ritual pledging. Competition elements included are social support, pharmacotherapy use, cash prize incentives and the use of a dedicated website and iPad application. A pre-test post-test will be combined with process evaluation to evaluate if the competition results in triggering mass-quitting, utilisation of pharmacotherapy and in increasing sustained smoking cessation and to get a comprehensive understanding of the way in which they contribute to the effect. The present study is the first to describe how knowledge about cultural practices and principles can be combined with proven cessation support into a smoking cessation contest. The findings from this study are promising and further more rigorous testing is warranted.

## Background

Tobacco kills nearly 6 million people worldwide, and causes hundreds of billions of dollars of economic damage each year [1]. New Zealand (NZ) has had a progressive tobacco control programme since 1994 with sustained strong tobacco control policies, for example smoke-free environments, increasing tax on tobacco, and public health programmes, and since 2000 an increasing range of cessation support, such as, the national Quitline [2]. This comprehensive programme has led to a drop in daily smoking prevalence from 26.6% in 1997 to 19.2% in 2009 [3,4]. However, each year 4500-5000 people are still killed by smoking or exposure to second-hand smoke [3]. Considerable inequity exists across the population with smoking prevalence among Māori at 45.1% and Pacific Island people at 30.3% compared to New Zealand European at 19.7% rates [3].

The government of New Zealand has set an ambitious goal for the country to be smokefree, defined as “a smoking prevalence of less than 5%, with tobacco being difficult to obtain and children not exposed to smoking”, by 2025. To achieve this, new and innovative strategies are needed to bring about rapid reduction in smoking prevalence. Generic population tobacco control programmes, however, have increased the gap between different SES groups and ethnic groups [5]. Therefore there is a need for programmes specifically focused on disadvantaged population groups.

Interventions that have shown promise internationally are stop smoking competitions where usually individuals who smoke stop for a chance to win a prize of cash or products. Quit and win competitions have run all over the world since the early 1980s [6] with long term quit rates ranging from 8% to 20% at 12-months [7]. Short term quit rates at the end of the competition have been as high as 66% [8]. Only a few quit and win competitions have focused on disadvantaged population groups. However, one quit and win competition aimed at low-income smokers in the United States had significantly higher overall quit rates in the treatment group with 23% (compared to 9% in the control group) still quit at 12-months [9]. Māori and Pacific Island people in NZ are overrepresented among lower socio-economic groups [10,11]. A quit and win competition was piloted in 2000 in the Hawke’s Bay region of New Zealand and achieved quit rates of 40% at 12 months follow-up [12]. The competition included a high proportion of Māori (32% compared to 22% of the total Hawkes Bay population).

Given NZ’s heightened urgency to increase quitting on a mass scale, and the positive potential for quit and win competitions to be attractive to and more effective at bringing about cessation among smokers from lower socio-economic groups it is time to test quit and win competitions for Māori and Pacific Island people [13]. We propose a quit and win competition which is aligned more with Indigenous people’ cultural principles and beliefs. The main aim of this paper is to describe how knowledge of Indigenous people’s practices and principles can be incorporated with proven effective smoking cessation support into a culturally appropriate cessation intervention WERO (WERO in the Māori language means challenge). Included in the aim is describing identified cultural principles and practices that can be used in a cessation competition and describing identified effective cessation elements that could be incorporated. A final aim of the paper is to describe the WERO study protocol.

### Cultural principles and practices

Designing public health interventions consistent with the cultural beliefs and practices of target populations is believed to lead to better receptivity, acceptance and salience of health information and programs [14].

#### Competitiveness

The indigenous people of NZ are collectively called Māori but there are many tribes within the Māori nation. Tribal identity is strong and historically marked by inter-tribal rivalry and competition, which carries on in modern times [15,16]. This rivalry and competition is not a means of excluding others, rather it develops and maintains a sense of collective unity, loyalty and belonging within the group [16]. Kapa haka (traditional Māori performing arts) regional and national competitions are an important way to construct a secure Māori identity and the skills learned can be transferred into other areas of life [17]. Māori and Pacific Island peoples have higher participation rates in sport, recreation and physical activities than other ethnic groups in NZ [18]. For instance, kapa haka contests are well-attended and popular. Te Matatini National Festival which is held every two years attracts up to 30,000 participants and visitors [19]. Other group competitions include Top Town, where communities compete for their town, and inter-marae (traditional tribal meeting place) sports events, to celebrate family values, strengthen kinship and assist in maintaining cultural values and knowledge in an atmosphere of friendly competition and healthy lifestyles [20]. Among Pacific Island people, competitive sports such as kilikiti (a Samoan form of cricket) are popular, with high participation rates [21]. These contests incorporate competitiveness with cultural elements and encourage community participation, all of which are key components for effective health interventions for Indigenous people [22]. Furthermore, competitions have also been used to encourage behaviour changes, such as weight loss (for example [23]) and seatbelt usage among teenagers (for example [24]).

#### Family centred

Like many other Indigenous people, Māori and Pacific Island peoples are whānau (family) centred, where the wellbeing of the family, church, extended family and culture is often placed above personal health. The NZ government *Whānau Ora* policy was developed to establish and recognise the centrality of the family in the delivery of health and social services. Recently, health provider organisations with a sole focus on Pacific Island peoples have been included in the *Whānau Ora* programme [25]. *Whānau Ora* is an inclusive approach to providing health services to families across New Zealand. It builds on the strengths and capabilities present in families as a whole, rather than focusing separately on individual members and their problems [25,26].

A smoker’s motivation to smoke is affected by environmental, social, economic and personal determinants [27]. Māori smoking cessation services provide support to individuals and families to quit together. Support is typically extended to other smokers in the presenting individuals’ friendship network, household or work environment [28]. Group cessation approaches therefore align with Māori and Pacific Island whānau centred values and practices and increase the number of smokers assisted at a time.

#### Fundraising

Another common Indigenous culturally embedded practice is fundraising. Both Māori and Pacific Island cultures organise and participate in fundraising for schools, churches, cultural events and competitions, sports, marae and family reunions [29]. Voluntary activity, fundraising, is for many Māori and Pacific Island people an act of service to their whānau, and iwi (tribe) and one way of fulfilling family and social obligations and responsibilities. This activity is central to identity and to the maintenance of culture and traditions. In 2001, Māori were more likely than non-Māori to have been involved in unpaid activities outside the household [30]. Many Pacific Island people see volunteering as a moral and ethical responsibility, and a cultural duty that is passed on through traditional roles and responsibilities to the collective group and their family [30,31].

### Effective elements of smoking cessation competitions

Most quit and win contests include a cessation support programme in addition to the contest [32]. A few quit and win studies have investigated the effectiveness of general cessation support, such as pharmacological support, social support, use of incentives, and technology, in a quit and win context [33-36]. Elements of a smoking cessation competition are considered effective when they significantly impact the chances of short-term and/or long-term abstinence.

#### Pharmacological support

In general, the use of any type of pharmacological support is likely to increase cessation rates [32,33,37-39]. Nicotine Replacement Therapy (NRT) increases the chances of successfully stopping smoking by 50% to 70% [39]. Similar findings have been found for Māori: smokers who took bupropion doubled their cessation rates in comparison with the placebo group [40].

When comparing NRT use with or without competition, Maheu et al. [41] found that combining contest and NRT led to a significant increase in number of smokefree weeks, in comparison with NRT without contest. However, another study found that there was no significant long-term difference in cessation rates between those quitters who used no pharmacological support and those who did [8].

#### Social support

Social support, given by family, friends and co-workers, has a positive influence on smoking cessation in general [42,43] and has a particularly significant impact when combined with quit and win competitions [33,34,37,44,45]. Cessation rates are higher for contestants with a designated support person compared with those without [34,44]. One study found that 60% of their contestants utilised a designated support person, which reflects the importance of this type of support [44]. The type of relationship that the support person had with their smoker has an influence as well where having a spouse or partner as a buddy was most effective [37].

#### Incentives

Cash incentives have been shown to boost motivation to quit [45,46]. Although the effects on long-term abstinence are not yet clear, there is a short-term effect [32]. For example, in one study 57% of the participants stated that the chance of winning a cash prize had helped them to remain abstinent [46].

#### Technology to support quitting

There has been a rise in use of e-Health, such as internet, smartphone and tablet PC applications (apps), to prompt and support behaviour change to improve health. Such technologies have the potential to reach large numbers of people [47,48]. Internet-based social support groups can connect people in disparate locations and can provide support at all times of the day, at a minimal cost [47,49]. Often posts on website message boards allow quick responses by peers, indicating that social networking may be beneficial to prevent relapse by smokers trying to quit, especially in comparison to the time it may take to seek professional help [49].

In the area of smoking cessation, the internet has provided a platform for interactive support. One such social network for tobacco users, QuitNet, has a large number of members who persist over time, even after quitting. This shows that social networking may prevent relapse for a lengthy period of time [48]. The use of the internet for smoking cessation is most effective when there is a high frequency of visits to the website. A randomised controlled trial which tested the effectiveness of internet use, in conjunction with other smoking cessation interventions such as NRT, found that the number of times participants used the website per week was significantly related to abstinence both at the end of the treatment period and at the 6 month follow up; yet purely access to the website was not [50]. Smartphone (mobile phones which can also run computer programmes or apps) and tablet PC apps have also been used to assist with smoking cessation. However, while there is a large amount of research about the use of other types of technology to promote behaviour change, there is very little research in this area, given how recently apps have been introduced.

### Integrating cultural and smoking cessation elements into the WERO intervention

Incorporating Māori and Pacific Island people’s inherent interest in competition into a cessation intervention could potentially increase attractiveness of the intervention and thereby increase uptake and retention. However, to the best of our knowledge, no Indigenous-informed quit and win contest has been trialled and published. The vast majority of Quit and Win competitions pitch individuals against each other [7]. But because of the strong family-community centrality of many Indigenous peoples, group-, rather than individual-, based competition may be more appropriate. Therefore, the main part of the intervention was an inter-team contest where the team with the most quitters at end of competition won a prize.

In order to increase the effectiveness of the contest, other cultural and smoking cessation elements were also included. A contest that ties in with Māori and Pacific Island people’s practises of fundraising may be attractive. Benefitting their community may be a stronger motivator to quit than individual benefit. Therefore, in WERO, the winning prize did not go to the team participants, but rather an organisation or charity of their choice. This fundraising aspect is expected to appeal to participants’ existing sense of duty to raise funds for cultural or local community events and other needs. This may provide additional motivation over and above any motivation to quit for their own benefit.

Further, members of each team had their progress displayed on a public website. Lastly, given the substantial and well documented increase in quit success with the use of pharmacological support, these were also included in the intervention.

#### WERO intervention

WERO participants compete in teams of ten current smokers, the majority of which knew each other prior to the intervention, which boosts peer social support and enable the dynamics of whanaungatanga (a relationship through familial and shared experiences) to operate. Each team appoints a ‘coach’ whose role is to encourage their team and facilitate team meetings and activities. Criteria for the coaches are that they are non-smokers or ex-smokers, and that they are willing to support their team to quit over the contest period.

The team with the most smokefree members at the end of the competition wins. If multiple teams have the same number of smokefree team members, one winner will be randomly drawn by a computer random digit generator. The prize of $5000 goes to their nominated charity or community organisation. If a team member tries to cheat the competition, team members would continue to receive support to quit but they would be excluded from the prize draw.

WERO participants are encouraged and supported to use NRT, such as, nicotine patches, gum or lozenges, which in New Zealand can be obtained using a Quitcard for as little $5 for 8 weeks supply. They are also told about Champix (varenicline) and Zyban (bupropion) which are subsidised, but only available on prescription. The *New Zealand smoking cessation guidelines* recommend NRT be used for a course of at least 8 weeks [51], thus the WERO competition period will run for 3 months.

An interactive website and iPad app is used to strengthen the sense of team and inter-team competitiveness by making the smoking status of team members and the team as a whole publicly visible. To keep all teams up-to-date on their own and other team’s performances, weekly updates of smoking status are requested from the regional Coordinators. Teams and supporters are also able to post questions, comments or support, to the team page. Frequent interaction with the website should help reduce relapse, and will be encouraged with the use of a prize of $500 for the team that utilises their team page the most. In addition, the website and app provides information in the style of tips on quitting and relapse prevention. Participants’ questions or comments about withdrawal symptoms and trigger situations on their web page can also be answered and commented on by the study’s primary investigator, an expert in smoking cessation.

Although it would be preferable to develop the app for multiple operating systems (OS), in the interests of cost-containment it was decided to develop for one OS and form-factor for this pilot. Further, the study team did not have the capacity to test the performance of an app across the wide range of tablets available. The iPad was chosen over other types of tablets as it has a wide user base and high levels of usability compared to other tablet PC operating systems such as Windows and Android.

## Methods/Design

WERO is one project within a broader programme of research being conducted or commissioned by the New Zealand Tobacco Control Research Tūranga. The Tūranga (platform) aims to identify innovative interventions and policies that could dramatically increase quit rates to speed NZ towards Smokefree 2025, whilst also decreasing inequities in smoking prevalence between Māori and Pacific Island people and non-Māori non-Pacific Island populations. Tūranga projects are expected to produce results quickly thus limiting study design. Randomized controlled trials and in-depth cost-benefit analysis for instance are beyond the budget and time constraints of the Tūranga. Thus, WERO will be evaluated using a multi-method approach consisting of a pre-test post-test design to assess effectiveness and a process evaluation to assess the contribution of the included effective elements in the programme and participants’ progress and motivation.

### Locations

WERO will be trialled in three regions: in rural Northland, in an urban Auckland Māori community and in the urban Auckland Pacific Island community. Running WERO in three different communities allows for testing for fit and effectiveness in different contexts (urban, rural) and for different ethnicities (Māori and Pacific Island people). The communities were chosen for their large proportion of Māori or Pacific Island people with high smoking prevalence, and for the availability of support services, like community health workers and smoking cessation providers.

### Regional coordinators

WERO co-ordinators, an identified person at regional level who can facilitate local use of WERO, will be appointed for each region. A District Health Board (DHB) healthy lifestyles team have been subcontracted to promote WERO and recruit teams in Northland. An urban Auckland Māori authority Whānau Ora provider have been subcontracted to deliver WERO to their urban population, and a Pacific Island WERO Co-ordinator was employed to work with Pacific Island churches. In addition to implementing the intervention, the WERO co-ordinators will also act as a research assistant and collect data.

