### Measures

The main outcome will be biochemically validated smoking status at the end of the competition. Main analyses will be carried out on an intention-to-treat basis. Participants lost to follow-up will be assumed to be smoking. Since quit and win can have high rates of deception, smoking status will be assessed using CO tests pre and post contest. CO tests were chosen for pragmatic reasons, namely its low cost, ease of use and its availability for healthcare providers. It is limited however to detection of active smoking within the previous 2-5 hours only [52], but unfortunately other methods are cost-prohibitive [53]. The CO tests were used to determine which team will win the prize. Secondary outcomes will be self-reported point prevalence at 6 months follow-up, use of pharmacotherapy, duration until relapse, tobacco consumption, and activity on the website. Because there will not be any incentives for participants’ to be smokefree at 6-months follow-up, the risk of deception is lower than at end of competition. Therefore, self-reports was considered sufficient. Furthermore, not doing a CO test at 6 months was also about reducing research burden for participants and research assistants, and using self-report enabled follow-up to be conducted by telephone.

At baseline and 3 months follow up exhaled CO will be measured using a Bedfont Smokerlyzer CO monitor. The amount of CO in ‘end-expired air’ is a good approximation for the concentration of CO in the blood and exhaled CO levels will be higher in smokers than in non-smokers. There is however no agreement about what the optimal cut-off point is. Middleton and Morice [54] found a cutoff level of 6 ppm, which detected 94% of smokers and 96% of non-smokers in a respiratory outpatient clinic. In this study a relatively low cutoff point of 6 ppm will be used, because there is low air pollution in New Zealand [55].

At baseline, 3 and 6 months participants will be asked to complete paper-based questionnaires with 33 close-ended questions (Table 1). These questionnaires are used to determine the progress of the participants and to determine the short-term effects of the competition.

**Table 1 T1:** Questionnaire topics

**Category**	**Topic realms**
Demographic	Sex, ethnicity, age, marital status, education level, community service card (proxy for socioeconomic status)
Smoking behavior	Smoking status, amount smoked, time to first cigarette, previous cessation attempts and methods used.

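### The regional co-ordinators who implement WERO also collect its data, so the primary outcome is apparently recorded by people with an interest in the result, in a study with no concurrent control

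*Protocol article*

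**What the plan says.** The Regional coordinators section of the protocol article gives the co-ordinators two jobs: "In addition to implementing the intervention, the WERO co-ordinators will also act as a research assistant and collect data". The same section describes them as regional organisations or staff engaged for the programme itself. For one region it says: "A District Health Board (DHB) healthy lifestyles team have been subcontracted to promote WERO and recruit teams in Northland". In the other two regions, a Māori Whānau Ora provider is contracted to deliver WERO and a Pacific Island co-ordinator is employed to work with churches.

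Under Measures, the primary endpoint is fixed as follows: "The main outcome will be biochemically validated smoking status at the end of the competition". The same readings settle the contest: "The CO tests were used to determine which team will win the prize". Under WERO intervention the rule is: "The team with the most smokefree members at the end of the competition wins". The prize does not go to individuals: "The prize of $5000 goes to their nominated charity or community organisation". During the contest the public scoreboard also depends on the co-ordinators, since "weekly updates of smoking status are requested from the regional Coordinators".

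At 6 months smoking status is self-reported without a CO test. One reason given is "reducing research burden for participants and research assistants, and using self-report enabled follow-up to be conducted by telephone". Measures and Discussion both treat false reporting as a risk that comes from participants. The limitations paragraph of the Discussion does not mention that delivery and data collection are in the same hands.

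**The concern.** Assessors who implement the programme have a natural interest in its success. The primary endpoint is apparently in their hands, and they also report their teams' standing every week during the contest.

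A CO monitor leaves limited room for judgement, but some remains. By the article's own account under Measures, the test detects smoking only over the previous 2 to 5 hours, so the hour of the appointment matters. A breath near 6 ppm can be repeated, and a displayed number has to be transcribed.

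In a randomised comparison with common assessors, leniency would fall partly on both arms. WERO is an uncontrolled pre-test post-test study whose sample size is set against an external Quitline rate of 24%. Any leniency therefore adds directly to the estimated quit rate and can be read as programme effect. The 6-month self-report has no biochemical check. The article justifies this by the absence of a prize at that time, which does not deal with a wish to give a welcome answer to someone connected with the programme.

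**Working it through.** **Inputs, all from the protocol article.** Power calculations: reference rate 24%, target 35%, one-sided 5%, 80% power, no design effect, about 100 needed, 150 recruited. Measures: intention to treat, with those lost to follow-up counted as smoking, so the denominator is 150. Team participants: 15 teams of ten.

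**Step 1: reproduce the plan's figure.** One-sample test of a proportion against a fixed 24%, normal approximation:

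n = [(1.645·√(0.24·0.76) + 0.842·√(0.35·0.65)) / 0.11]² = 100.7

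This agrees with the stated figure of about 100. The benchmark therefore behaves as a fixed external rate with no second arm.

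**Step 2: expected counts with 150 analysed.** At 24%: 0.24 × 150 = 36 quitters, leaving 114 smokers. At 35%: 0.35 × 150 = 52.5. The gap is 16.5 people, or 16.5/15 = 1.1 per team.

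**Step 3: threshold for success.** Exact binomial test, n = 150, p₀ = 0.24: P(X ≥ 45) = 0.055 and P(X ≥ 46) = 0.037. The critical count is 46 (46/150 = 30.7%), which is 10 above the expected 36. At a true 35% the power of this rule is 0.885.

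**Step 4: sensitivity to misrecording.** Suppose the true quit rate is 24% and a fraction f of true smokers is recorded as abstinent. The recorded rate is q = 0.24 + 0.76f, and the chance of a false success is P(X ≥ 46) with n = 150 and rate q. The values of f are assumptions; the article gives none.

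| f (assumed) | q | extra recorded quitters (114f) | chance of false success |
|---|---|---|---|
| 0 | 0.240 | 0 | 0.037 |
| 2% | 0.255 | 2.3 | 0.09 |
| 5% | 0.278 | 5.7 | 0.24 |
| 10% | 0.316 | 11.4 | 0.63 |

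To move the expected count from 36 to 46, f must be 10/114 = 8.8%. To produce the whole difference between 24% and 35%, f must be 0.11/0.76 = 14.5%.

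**Step 5: who measures.** The Regional coordinators section makes the co-ordinators the research assistants who collect data. Measures links omission of the 6-month CO test to research-assistant burden. No other assessor is named. That co-ordinators take the 3-month readings and make the 6-month calls follows by inference; the article does not say so directly.

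**The case against.** The strongest reply is that the endpoint leaves little discretion. It is a number on a named monitor against a fixed cut-off, and repeating a breath matters only for borderline readings. Exploiting the 2 to 5 hour window also needs the participant to abstain beforehand, which is largely the participant deception that the article already discusses. This stands as a limit on the size of the bias, but does not remove it.

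The misrecording fractions are assumed, the exact test is this review's choice, and 24% appears only in the power calculation. All of that stands, so the table is a sensitivity and not an estimate. A condensed article may also leave repeat-breath rules, call scripts and checks of readings to the full protocol. Their absence is not held against it; the point rests on the dual role, which the article fixes. Delivery through existing providers is deliberate, under stated budget and time limits, and 6-month status is only a secondary outcome.

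A reader might infer more than the documents support:

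- **That participants report at 6 months to the person who coached them.** Coaching belongs to 15 separate team coaches, and no section says who makes the calls.
- **That tracing likely quitters harder inflates the rate above the truth.** Those lost count as smoking, so an untraced smoker is classified correctly and extra tracing only recovers true quitters.
- **That co-ordinators gain from the prize.** It goes to a charity or community organisation, and no payment for results is described. Their interest is inferred from their role.

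**Conclusion.** The concern holds as a risk of bias. The article assigns data collection to those who implement WERO, and the same 3-month CO status serves as primary endpoint and prize decider. With no concurrent control, assessor leniency would pass straight into the quit rate.

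The margin is small in absolute terms: 10 people among 150 separate the expected count at 24% from the rejection threshold. It is less small as a rate, since 8.8% of true smokers would have to be misrecorded to move the expected count that far. Even so, 5% misrecording would raise the chance of a false success from 0.037 to 0.24.

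This rests on four assumptions: the co-ordinators are the assessors, the result is judged against 24%, participants are independent (as in the plan's own power calculation), and the misrecording fractions are illustrative. A reader might take the figures as evidence that readings were or would be misrecorded; nothing in the article shows that. The matter is worth correcting because the correction is cheap, and it is not a fatal flaw.

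**What to change.** Keep the co-ordinators as testers and move the classification away from them.

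1. At 3 months, count the first valid CO reading. Photograph every display with the participant ID and send it to the central study team, which classifies smoking status and declares the winner.
2. Have the central team make the 6-month self-report calls, using a fixed script.
3. State in the limitations that the co-ordinators both deliver the programme and collect its data. Appointment timing within the CO detection window should be mentioned there, because steps 1 and 2 do not control it.

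Exchanging co-ordinators between regions is not recommended. It would have competitors testing one another's teams, would leave the shared interest in a high overall rate, and could weaken the cultural fit on which the study is built.

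The cost is one photograph per test, a little central work, and possibly a slightly lower 6-month response to a less familiar caller. No new assay and no control arm are needed.
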